### Power calculation

An a priori power analysis indicates that a sample size of 90 would be required to detect a significant difference between groups with a medium effect size (*f* = .30) on primary outcome variables, with a power of 0.8 and a default alpha of .05, using the planned 2 X 2 mixed analysis of variance. Our goal for recruitment is therefore to continue until we reach 90 with data at both time points (i.e., 45 in each condition).

### Data collection

Data will be collected via survey by researchers either in-person or online when in-person data collection is not feasible. Participants will be allocated a study code so that no identifying information is collected with the surveys. The initial (T1) survey will be collected when participants first engage in social prescribing (i.e., when they begin to meet with the Link Worker, but are yet to attend a group or have only recently started attending a group activity). Participants will then be followed up 8-weeks later (T2). The number of group activities a participant joins during the 8-week period is up to the discretion of the participant and Link Worker, however, we expect that this will typically be just one new group. Surveys will be collected from the TAU participants across the same time interval of 8 weeks, and they will continue to receive primary care treatment as usual. Participants will be reimbursed with AUD $40 vouchers at T1 and T2. Non-identified service audit data will also be collected by researchers from the Link Workers to gain an overall sense of the total number of program referrals and the different referral pathways, as well as general demographic characteristics.

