**Methods:**

Ninety participants experiencing loneliness recruited from primary care services and community centres across five sites in Southeast Queensland will be assigned to one of two conditions (SP, TAU) and assessed at two timepoints (baseline, + 8 weeks). Individuals will be aged 18 years and over, have sufficient English language skills to provide consent, and at the time of recruitment they will not be experiencing acute symptoms or social issues that require urgent intervention. Primary outcomes are loneliness, mental well-being, and health service use (total number of GP, hospital, and allied health visits in the past 3 months). Secondary outcomes will assess social group processes, including number of important social groups, new group identification, multiple identity compatibility, and group-based support and emotion regulation.

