**Discussion:**

This study will provide comprehensive data about the extent to which, and how, social prescribing to community-based group activities may help people to feel less lonely, more socially integrated, and healthy over the first 8 weeks. If effective, this social identity-informed model of social prescribing can be disseminated in communities across Australia.

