## Methods

### Design and participants

While a randomised controlled design would be the strongest methodology, it requires participants to be interested and available to attend sessions with a link worker and then group activities as part of the social prescribing intervention if they are allocated to the treatment condition. It would be difficult to retain participants in social prescribing who are not interested and/or available, and conversely, it would be unethical to withhold social prescribing from participants who are interested and available, given evidence that it is potentially effective in managing loneliness. Accordingly, as shown in Fig. 2, our study will have a non-randomised controlled (parallel) design, with a social prescribing condition (SP) and a primary care treatment as usual (TAU) condition.

This research will take place in 5 sites in Southeast Queensland where social prescribing is offered, using a combination of GP and community centre models. The sites are in areas with diverse populations in terms of socioeconomic and cultural backgrounds: a community centre in a southern suburb of Brisbane, a GP clinic in the same suburb, a GP clinic in a southwestern suburb of Brisbane, a community centre in a northern suburb of Brisbane, and a combined GP and community centre in a regional city located about an hour’s drive south of Brisbane.

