*Social Prescribing participants* (SP) will be adults aged 18 and over, experiencing loneliness or social isolation who are eligible for referral to the social prescribing programs at these sites. Local General Practitioners and Allied Health Professionals expected to be the most likely referral pathway. Recruitment will be promoted through the authors giving talks to referring agents and through project steering meetings. Participants will have sufficient English language skills to be able to provide consent to participate in the research. We expect them to range in age, and to represent a variety of cultural and ethnic groups. Exclusion criteria are that the individual reports acute symptoms (such as suicidal ideation, manic or agitated behaviour, or intoxication), or an acute social issue (such as domestic violence or housing crisis that would need to take priority), that would interfere with their capacity to engage with SP. Such individuals will be directed by the Link Worker to a more suitable service. Link Workers will refer clients who indicate an openness to participating the study to the researchers who will contact individuals to confirm their consent to participate in the study.

*Treatment as Usual participants* (TAU) will be selected from GP clinics in the same locations as the social prescribing programs and will meet our inclusion and exclusion criteria. A staff member within each of these services will identify frequent attending patients who will be contacted by telephone by the researchers and invited to participate in the study. Frequently attending patients will be defined as patients attending the practice 12 or more times each year over a two-year period who have not already been referred to a social prescribing scheme. These parameters remove patients attending frequently for short-lived medical needs, such as a pregnancy. We will assess for baseline differences between the conditions and statistically control for any variables that are found to differ significantly at baseline.

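### The social prescribing arm's baseline survey may be taken after group attendance has begun, so T1 is not a pre-intervention value for every participant in that arm

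*Protocol article*

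**What the plan says.** The Abstract has participants "assessed at two timepoints (baseline, + 8 weeks", so T1 is the baseline. Data collection then fixes its timing in the SP arm: "The initial (T1) survey will be collected when participants first engage in social prescribing". By this the article means that meetings with the link worker have begun and that participants "but are yet to attend a group or have only recently started attending a group activity". T2 follows 8 weeks after T1, whatever the date of the first group session. For the comparison arm, "Surveys will be collected from the TAU participants across the same time interval of 8 weeks".

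The Design and participants section treats both components as the intervention, since people would "attend sessions with a link worker and then group activities as part of the social prescribing intervention". It also describes the route into the study: "Link Workers will refer clients who indicate an openness to participating the study to the researchers", who then make contact to confirm consent. TAU patients must not already have been referred to a social prescribing scheme. The same section plans to control statistically for variables that differ significantly between the conditions at baseline.

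The Abstract says the study will show how far people come to "feel less lonely, more socially integrated, and healthy over the first 8 weeks". The main Discussion expects the improvement to appear between the two assessments.

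**The concern.** The planned comparison is the change from T1 to T2 in SP against the same change in TAU. It needs a T1 that precedes the intervention in both arms. The timing rule secures that for TAU but not for SP, so the difference between conditions does not cancel the problem. Four things are at stake for SP participants who are already attending:

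- Whatever they gained before T1 is not part of their T1–T2 change.
- They can list the new group at T1, so the number of important groups may already contain the gain that the process model is meant to explain.
- T1–T2 is not their first 8 weeks in the group, although that is the period the Abstract names. For those not yet attending at T1, exposure to the group by T2 is less than 8 weeks.
- If a psychosocial score differs between conditions at T1 and is therefore adjusted for, part of that difference may be an effect of the intervention. The design is not randomised, so this adjustment is one of the main safeguards against confounding.

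A late T1 is plausible under the described procedure, because the link worker's referral and the researchers' consent call both come before the survey. A pre-exposure value that was never collected cannot be recovered in the analysis.

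**Working it through.** **Step 1. Reproduce the planned sample size.** Inputs from the Power calculation section: f = 0.30, power 0.8, alpha 0.05 (taken as two-sided), 90 participants with data at both time points, 45 per condition. For two equal groups d = 2f = 0.60. A two-group F test has noncentrality N × f² = 90 × 0.09 = 8.1 on 1 and 88 degrees of freedom, which gives power 0.804. The smallest even N that reaches 0.80 is 90, so the stated figure reproduces as a plain two-group comparison with d = 0.60. That is the base used below.

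**Step 2. When does a late T1 shrink the contrast?** Let B(t) be the mean benefit t weeks after the group starts, and suppose a participant starts e weeks before T1. The recorded change is B(8 + e) − B(e), while the benefit over the first 8 weeks is B(8).

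- Linear benefit, B(t) = bt: the recorded change is b(8 + e) − be = 8b, which equals B(8). Nothing is lost. A participant who starts k weeks after T1 records only b(8 − k), which is less.
- Front-loaded benefit (early weeks count for more): the recorded change is below B(8). At the extreme, with a plateau so that B(8 + e) = B(8), the whole of B(e) is lost.
- No early benefit, B(e) = 0: nothing has been gained by T1 that the change could miss.

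The direction therefore depends on the shape of B, which the article does not give.

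**Step 3. Illustration under the plateau case.** Let s be the share of SP participants already in a group at T1, and a = B(e)/B(8) the fraction of their effect present by then. The retained effect is d = 0.60 × (1 − s × a), with the SD unchanged. The article gives neither s nor a, so both are assumptions.

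| s | a | 1 − s × a | d | Power at N = 90 | N for 80% power |
|---|---|---|---|---|---|
| 0 | – | 1 | 0.600 | 0.80 | 90 |
| 0.25 | 0.10 | 0.975 | 0.585 | 0.78 | 94 |
| 0.25 | 0.25 | 0.938 | 0.562 | 0.75 | 102 |
| 0.25 | 0.50 | 0.875 | 0.525 | 0.69 | 116 |
| 0.50 | 0.10 | 0.950 | 0.570 | 0.76 | 100 |
| 0.50 | 0.25 | 0.875 | 0.525 | 0.69 | 116 |
| 0.50 | 0.50 | 0.750 | 0.450 | 0.56 | 158 |

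**Step 4. What would excluding late T1 surveys cost?** At s = 0.25 to 0.50, between 0.25 × 45 = 11.25 and 0.50 × 45 = 22.5 SP participants would leave the comparison. With 34 or 22 SP participants against 45 TAU, the noncentrality is d² × n₁n₂/(n₁ + n₂) = 0.36 × 34 × 45/79 = 6.97 or 0.36 × 22 × 45/67 = 5.32. Power at d = 0.60 is then 0.74 or 0.62. Exclusion without replacement can lose about as much power as the problem itself.

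**The case against.** The strongest reply is that the direction is not established. T2 is tied to T1, so an early starter still has 8 weeks between surveys. Step 2 shows that under linear accrual this person's change is no smaller than the first-8-weeks effect. This stands. A reader might infer that the SP effect is necessarily biased towards zero, and the article does not support that.

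Second, the shares and early fractions are invented, and large early fractions fit poorly with wording about first engagement and a recent start. This stands too, so the power range is no estimate. It also treats d = 0.60 as the standardised contrast that T1 affects. If the power calculation concerned a comparison at T2 only, T1 timing would not reduce it. If it concerned change, d would depend on a pre–post correlation that is not given.

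Third, not everything is affected equally. The Abstract counts health service visits over the past 3 months, so T1 is mostly pre-exposure on that measure for a recent starter, although the Measures section words the period differently. T1 outcomes enter the mixed model as repeated responses, and many possible covariates, such as demographics, cannot be changed by joining a group. The adjustment concern is therefore limited to T1 psychosocial scores.

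Fourth, exact visit windows are commonly left to a full protocol. This stands less well: the article does not merely omit a window, it expressly allows T1 after attendance has started, in one arm only.

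**Conclusion.** The point holds as a defect in the timing rule. For some SP participants the rule accepts a baseline taken after exposure to the group, with no counterpart in TAU. Pre-T1 gains are then missing from the change, the T1 group count may include the new group, the interval is not the one the Abstract names, and adjustment for T1 psychosocial scores may remove part of an effect.

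The size is unknown. Attenuation requires front-loaded benefit and some participants surveyed late. If both apply, with 25–50% starting early and 10–50% of the effect present at T1, power runs from 0.78 to 0.56 instead of 0.80. That range rests on assumed inputs, a plateau in benefit, an unchanged SD and d = 0.60 as the affected contrast. It supports neither a stated percentage loss nor a claim that the trial is underpowered for this reason. The case for acting is that the remedy is cheap and that the missing value cannot be recovered later.

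**What to change.** - Change the Data collection section so that T1 in the SP arm is collected before the first group session and as close as possible to the first link-worker meeting.
- Record three dates for every SP participant: first link-worker meeting, first group session and T1.
- Keep any participant whose T1 slips past the first session in the intention-to-treat analysis. Dropping them would depart from the all-available-data analysis in the Analysis section, select on speed of engagement, and cost the power shown in Step 4.
- Add a sensitivity analysis restricted to SP participants whose T1 preceded their first group session.

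The cost is one procedural sentence, three dates and one extra analysis. The downside is tighter scheduling of T1, and possibly a few late-referred clients who cannot be enrolled in time.

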### Measures

***The primary outcomes are loneliness, wellbeing, and health service use, and these will be assessed in both T1 and T2 surveys.***

*Loneliness* will be assessed via the 8-item brief UCLA Loneliness Scale [45] (e.g., ‘how often do you feel left out?’), in which responses are made on a 4-point scale (where 0 = *never*, 1 = *rarely*, 2 = *sometimes*, and 3 = *often*). Items are summed to produce a total score ranging from 0 to 24.

*Wellbeing* will be measured using the 14-item Warwick Edinburgh Mental Wellbeing Scale [46]. The items are positively worded and ask respondents how often they have experienced various psychological states over the past 2 weeks (e.g., ‘I’ve been feeling relaxed’) on a 5-point rating scale (where 1 = *none of the time* to 5 = *all of the time*). Scores are summed to produce a total score in the range from 14 to 70, with higher scores corresponding to a higher level of mental well-being. The WEMWBS is psychometrically robust in general populations, with excellent internal consistency (α = 0.91) and good test-retest reliability (*r* = .83) [46].

*Health Service Use* will be measured by the self-reported total number of visits that participants make to hospital, community mental health services, counsellor, psychologist, psychiatrist, social worker, GP (in person, over the phone, or via home visit) over the course of the study (adapted from the measure used in [47]). In addition, respondents will be asked to rate their current health on a single 5-point scale (where 1 = *very poor* to 5 = *very good)*.

Secondary outcomes are process measures by which the social prescribing intervention is expected to produce effects on the primary outcomes: group memberships and identities, new group identification, former and new group compatibility, and group-based psychosocial resources of social support and emotion regulation.

*Group memberships and identities* Participants will be asked to list up to six groups that they are members of and rate the importance of each on a 7-point scale (where 1 = *not important* to 7 = *very important).* From this, the number of important groups (i.e., those rated 5–7) will be derived (see [34], p. 350–351).

*New group membership and identification* Social identification with the (first) new group that the participant has joined through the social prescribing program will be measured by 4-items rated on a 5-point scale (where 1 = *strongly disagree* to 5 = *strongly agree* [48];).

*Group compatibility* will be measured by averaging 2 items: ‘Being a member of my new group/s is compatible with being a member of my other groups’ and ‘The norms and values of my various groups are compatible with each other’, both rated on a 5-point scale (where 1 = *strongly disagree* to 5 = *strongly agree* [34];, pp. 349–350).

*Group-based psychological resources* are defined as social support received and provided, measured by an average of scores on 2 items from [43]: ‘I get support from people in my new group’ and ‘I provide support to others in my new group’. Each is rated on a 5-point scale (where 1 = *strongly disagree* to 5 = *strongly agree*). Emotion regulation was measured using a 12-item version of the Emotion Regulation of Others and Self measure [49], which has been validated in previous research using a large sample representative of the UK population [42]. In this study, we use the two interpersonal EROS subscales assessed by 3 items each: extrinsic affect improving (e.g., ‘I discussed someone’s positive characteristics to try to improve how they felt’) and extrinsic affect worsening (e.g., ‘I explained to someone how they had hurt myself or others to try to make the person feel worse’).

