The social identity approach argues that a lack or loss of group memberships is a significant determinant of loneliness [42]. Moreover, this lack of group memberships is often a particular problem for people who experience economic disadvantage, disability, or chronic health problems [3]. SIMIC suggests that here loneliness can result from the fact that those who are marginalised in this way may have limited existing group memberships and identities and therefore few, if any, psychosocial resources to draw upon in stressful times. Here, we are considering the lonely person’s referral to a social prescribing program to be a transitional period whereby they develop a relationship with a link worker and become engaged in a meaningful group activity. The model predicts that, to the extent that the person identifies with their new group, they will be able to access group-based psychosocial resources. Two psychosocial resources that appear most relevant to the experience of loneliness are social support given and received, and emotional sharing with other members of the group. Support given and received have been shown in previous research to mediate the relationship between group identification and (lower) stress and life satisfaction [43]. Group-based emotion regulation is predicted to decrease individuals’ experience of loneliness — itself a negative emotional state [1]. Indeed, research suggests that emotion regulation plays a key role in the dynamics of loneliness [42, 44].

Thus, the study will test the extent to which joining one or more new groups through social prescribing initiatives (2), and the associated social identity gain, provides participants with opportunities to give and receive support from others, and to regulate their own and others’ emotions (5), which are expected in turn, to decrease loneliness, decrease inappropriate health service use, and increase wellbeing (6). In addition, those individuals who are fortunate to have existing group memberships and identities before joining the social prescribing program are expected to report positive outcomes to the extent that they maintain their former groups and identities (3), and that these are compatible (4) with the new group memberships and identities gained through the social prescribing initiative.

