The proposed study responds to recent calls for more research into social prescribing (e.g., in the 2021 QLD Parliamentary Inquiry into social isolation and loneliness, the 2020 Royal Australian College of General Practitioners / Consumers Health Forum Round Table report, and the 2020 Friends for Good More than Medicine report). It also addresses the need for high-quality evidence to evaluate social prescribing in an Australian context. We will evaluate the effectiveness of social prescribing, in comparison to GP treatment as usual (TAU), in reducing loneliness, as well as its effects on wellbeing and health service usage across an 8-week period.

We hypothesise that participants who participate in social prescribing will show significant improvements in loneliness and wellbeing and lower use of health services relative to those in the TAU condition. Second, the study will test the processes through which observed outcomes occur, with a focus on evaluating the two pathways in the expanded SIMIC-based model to determine whether number of important social groups, new group identification, old and new group identity compatibility, and group-based psychological resources (support given and received, and emotion regulation) are implicated in reduced loneliness and health service use and increased wellbeing over the course of the study.

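### The score taken from the group list does not separate kept former groups from the new social prescribing group, so the maintenance pathway has no variable of its own

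*Protocol article*

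**What the plan says.** The Background of the protocol article makes two separate predictions. The first concerns gain: "joining one or more new groups through social prescribing initiatives (2), and the associated social identity gain" should open access to support and emotion regulation and so improve outcomes. The second concerns maintenance: people with existing groups are "expected to report positive outcomes to the extent that they maintain their former groups and identities (3" in the numbering of the model). The account of SIMIC in the same section draws the same line between identity continuity and identity gain. The closing paragraph of the Background then names the aim as "evaluating the two pathways in the expanded SIMIC-based model".

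In Measures, the group item reads "Participants will be asked to list up to six groups that they are members of and rate the importance of each", and the scoring rule begins "From this, the number of important groups" and counts those rated 5 to 7. As described, the item does not mark a listed group as former or new, and the rule does not take the social prescribing group out of the count.

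The other group measures are identification with the first new group joined through the programme, compatibility between new and other groups, and support received and given in the new group. The Analysis section lists the variables of the structural equation model: group membership, new group identification, compatibility, help given, interpersonal emotion regulation and the outcomes.

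**The concern.** A maintenance hypothesis needs a variable that moves when former groups are kept or lost. The count moves with both maintenance and gain, and in opposite directions when someone loses a former group while joining the prescribed one. An unchanged count can then mean that nothing happened, or that one group replaced another.

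What is at stake is the reading of the process model. If the count is related to loneliness or wellbeing at T2, the analysis as stated cannot say how far this reflects kept former groups, which is prediction 3, and how far it reflects the new group, which is prediction 2.

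**Working it through.** The article gives no figure on this point. Its one calculated figure, the sample size of 90, plays no part here.

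**Step 1: match each prediction to a score.**

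| Prediction (Background) | Score in Measures | Does it record the prediction? |
|---|---|---|
| 2, gain | New group identification (4 items, first new group) | Partly: strength of identification |
| 3, maintenance | None named; the count of groups rated 5 to 7 is the nearest | Not alone: former and new groups are summed |
| 4, compatibility | Two-item mean | Yes, but it measures fit between groups, not whether former groups were kept |

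**Step 2: what the count can identify.** Let B be the important former groups at T1, K the number of these still held and important at T2, and G = 1 if the new social prescribing group is listed and rated 5 to 7 (otherwise 0). Assume at most one new group (Data collection expects typically one), no other groups gained, and no social prescribing group in the T1 list. Then

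- T1 count = B, from 0 to 6
- T2 count = K + G, with K from 0 to B and a ceiling of 6

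Possible pairs of counts for B = 0, 1, 2, 3, 4, 5, 6: 2 + 3 + 4 + 5 + 6 + 7 + 7 = 34.

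A pair has two explanations, (K = T2, G = 0) and (K = T2 − 1, G = 1), whenever T2 lies between 1 and B. The number of such pairs is 0 + 1 + 2 + 3 + 4 + 5 + 6 = 21.

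So 21 of 34 pairs are ambiguous. For example, 2 at T1 and 2 at T2 fits both keeping two groups with no important new one (K = 2, G = 0) and losing one while gaining the prescribed group (K = 1, G = 1).

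**Step 3: does new group identification resolve it?** If G were known, K would follow as T2 − G. The identification scale measures how strongly a person identifies with the first new group. It does not say whether that group was listed or rated 5 to 7. It can stand in for G in a model, but it does not reveal G.

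**Step 4: baseline timing.** Data collection allows T1 to be taken when a participant has recently started a group. The T1 count may then already contain the social prescribing group, so it is not reliably a count of former groups.

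**Step 5: illustration of size, on assumed inputs.** Assume a mean of 2 important groups at T1, retention of 0.8 per group, losses Poisson with mean 2 × 0.2 = 0.4, and an important new group with probability 0.5 to 0.8.

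- P(lose exactly one) = 0.4 × e^(−0.4) = 0.268
- P(lose at least one) = 1 − e^(−0.4) = 0.330
- Among those who lose a group, the share with no fall in the count = (0.268 / 0.330) × 0.5 to 0.8 = 41% to 65%
- Among all social prescribing participants = 0.268 × 0.5 to 0.8 = 13% to 21%

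With retention of 0.95, mean loss is 0.1, and the share of all social prescribing participants is 0.1 × e^(−0.1) × 0.5 to 0.8 = 0.0905 × 0.5 to 0.8 = 4.5% to 7%. None of these inputs comes from the article.

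**The case against.** The strongest reply is that the article has more than one group variable. New group identification, compatibility and new-group support all speak to the new group and enter the model separately from group membership. The ambiguity in Step 2 belongs to the count taken alone. This stands for gain. It does not supply a maintenance score, because none of those variables records what happened to former groups.

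A second reply is that the article condenses, and that variable construction is usually left to a fuller plan. Fig. 1 is not shown, and the scoring rule cites an outside source. Either might say how former groups are handled, and the article does not say that the count is all that will be taken from the lists. This limits how firmly the point can be put. But the article does state the scoring rule and does list the model's variables, and as stated they leave out one of its own predictions.

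A reader might infer two stronger things.

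- **That maintenance cannot be tested at all, or that the two pathways cannot be separated.** The documents do not support this. The limit lies in the derived score, not in the data requested. If the lists are recorded by name at both times, kept and new groups can be told apart. Repeated collection of the list is implied by the repeated measures models for secondary outcomes, although the article states T1 and T2 assessment explicitly only for the primary outcomes.
- **That the between-arm comparison of the count merely counts attendance at the intervention.** This is not supported either. A new group counts only if the participant lists it and rates it 5 to 7, and the Background treats a rise in the number of important groups as part of the intended mechanism.

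**Conclusion.** The point holds in a limited form. Prediction 3 is stated, but no score or model variable in the article captures maintenance, and the count of important groups cannot stand in for it.

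The firm part is the logic of Step 2: 21 of 34 pairs of counts are ambiguous under assumptions that favour the plan. A T1 list that already holds the new group, or more than one new group, makes the count less informative still. The percentages in Step 5 are illustrative only and vary widely with assumed retention.

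The consequence is small. It touches the secondary mechanism aim, and within it a prediction that concerns only participants with existing groups. The primary outcomes, their comparison between conditions and the sample size are unaffected.

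**What to change.** - Record the listed groups by name at T1 and T2, and say so for both conditions.
- Flag any group joined through social prescribing at both times, including one already started at T1. Otherwise simple matching would class it as a maintained former group.
- Derive the number of important former groups maintained (listed and rated 5 to 7 at both times) and the number lost. State how a group still listed at T2 but rated below 5 is classed.
- Enter the maintained count in the structural equation model for pathway 3, alongside new group identification for gain.
- Keep the total count of important groups as the secondary outcome. Reporting it also without the social prescribing group is an optional descriptive sensitivity analysis.

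The cost is matching names across two lists of at most six entries for about 90 people. No new questionnaire and no change in sample size is needed. If names were not kept at one of the two times, the article's successor report should say that prediction 3 was not tested directly.
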